#### Interim analysis

Intervention allocation will remain hidden for any interim analysis performed. Furturemore, As this is a minimal risk experiment, there will be no interim analysis or stopping instructions.

### Methods for additional analyses (non-adherence and missing data)

Missing data will be reported and links between results reviewed. depending on the extent of data missing an appropriate sensitivity analysis will be performed.

### Auditing

The auditors will follow a monitoring plan to verify that the clinical trial is conducted and that data are generated, documented, and reported in compliance with the protocol and the applicable regulatory requirements. Due to the nature of the educational intervention, there is no adverse event and no harm in this study. To our knowledge, the present study will not have any negative consequences. Every 6 months, we will send a report to the auditor. We will share the results of this study with keys Representative of the ethics committee and reviewers via presenting in related seminars.

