Current efforts to prevent the spread of STIs are insufficient and despite significant efforts to identify simple interventions for reducing high-risk behaviors, changing behavior remains a complex challenge [3]. Several reasons highlight challenges in sexual health education in particular STIs. The results of a review study show that, in general, Muslim women have poor knowledge about the signs and symptoms of STIs, how to prevent, diagnose, and treat them, in addition to many concerns. wrong concept. Negative attitudes towards people living with HIV/AIDS are widespread, and this attitude is strongly influenced by misconceptions and inadequate knowledge. Infected women tend to face more blame and judgment than men [12]. The fact that the mere existence of sexually transmitted infections (STIs) in Iran and other Muslim countries is considered taboo by the government and the public has created a state of denial, which is what some call “a health crisis behind the veil.” [13–15]. Furthermore, individuals’ access to effective resources has been hampered in many developing countries due to negative attitudes toward sexual health education, ineffective communication skills, insufficient educational materials, and a lack of knowledge [16].

Despite being prohibited in the religion of Islam, premarital and extramarital sexual relationships are by no means non-existent, and the scarce literature dedicated to sexual practice in Iran confirms this [16]. Moreover, the incidence of premarital sex has increased over the years [17, 18]. Iranians’ sexual health may be jeopardized as a result of receiving incorrect sexual information from the internet and other sources [19, 20]. Furthermore, discussing STIs is a cultural constraint and taboo [21].

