### Ethical approval

This protocol and the template informed consent forms will be reviewed and approved by the sponsor and Medical Ethics Research Center of Tarbiat Modares University (reference: IR.MODARES.REC.1399.039). with respect to scientific content and compliance with applicable research and human subjects regulations. The protocol, site-specific informed consent forms (Persian language), participant education and recruitment materials, and other requested documents—and any subsequent modifications—also will be reviewed and approved by the ethical review bodies. Subsequent to the initial review and approval, Ethical Committees (TMU) will review the protocol at least annually. The Investigator will make safety and progress reports to the TMU at least annually and within six months of study termination. These reports will include the total number of participants enrolled . . . and summaries of each stage of intervention [33].

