### Strategies to improve adherence to interventions

Women are required to be present at the study site in person to receive the intervention, and any missed sessions are recorded to check adherence. To improve adherence, training program times are flexible between 9am and 5pm each day (room availability permitting), are not required to be at the same time of day, and are not required on weekends. Participants will be arranged for a free visit with a trained midwife for genital examination and health counseling.

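### The Auditing section states as fact, before any data, that there is no harm, which conflicts with the promised safety reports and the minimal-risk label

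*Protocol article*

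**What the plan says.** The Auditing section of the protocol article states, giving the educational nature of the intervention as the reason, that "there is no adverse event and no harm in this study". The sentence after it is softer: "To our knowledge, the present study will not have any negative consequences".

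Four other places bear on this:

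- **Ethical approval:** "The Investigator will make safety and progress reports to the TMU at least annually and within six months of study termination". The article names no data source for the safety part.
- **Interim analysis:** "As this is a minimal risk experiment, there will be no interim analysis or stopping instructions".
- **Strategies to improve adherence to interventions:** participants are offered a "free visit with a trained midwife for genital examination and health counseling".
- **Engagement and retention:** the specialist is told which women are in the intervention group.

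The outcomes described are STI knowledge, vulnerability, prevention self-efficacy and prevention intentions, with self-reported preventive actions as secondary. The Instruments section describes the four-scale questionnaire, and the quantitative analysis section covers group comparisons over time. None of these sections mentions an unwanted effect.

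**The concern.** Whether an intervention causes harm is a question for the trial's data. A protocol may say that it expects little or none. Here the absence of harm is given as a fact, on a reason (the programme is educational) that covers only part of what participants go through.

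The article's own text suggests where unwanted effects could arise. It describes STIs as a taboo subject and says "Infected women tend to face more blame and judgment than men". It arranges a physical examination, and it discloses group membership by name to a third party. Distress and loss of privacy are plausible in that setting, though the article gives no rate for either.

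What is at stake is the content of the safety reports and of any later statement about safety. The Conclusion hopes to extend the programme to all at-risk women aged 18 to 48, so such a statement could be carried well beyond this sample. Staff who read that harm is ruled out in advance also have little reason to ask about it.

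**Working it through.** The article gives no harm rate or safety figure to reproduce, so the check sets its statements side by side.

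1. **Auditing against Ethical approval.** One says that no adverse event or harm exists. The other commits the investigator to safety reports at least annually. If the first is taken literally, the safety part of those reports is settled before the trial starts. If the reports are meant to inform the ethics committee, the first cannot stand as written.

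2. **Auditing against Interim analysis.** One says zero risk and the other minimal risk. Minimal risk is a classification made beforehand and is compatible with some harm occurring. Zero harm is a result.

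3. **The reason given against the procedures described.** The educational nature of the intervention is the only ground offered. The genital examination is not education, and passing on the names of intervention women is a confidentiality exposure tied to allocation. The ground does not reach either.

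4. **The conclusion against the data described.** Going through the sections:
   - Outcome measures: four scale scores and self-reported preventive actions.
   - Instruments: 40 Likert items on the four scales.
   - Quantitative analysis: repeated-measures comparisons and mean differences with 95% confidence intervals.

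   A score on any of these could be excellent in a woman who was distressed or whose privacy was breached. None can support a statement about harm in either direction.

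**Illustration only, not a figure from the plan.** Suppose harms were fully collected and none were seen in an arm of n women. The exact one-sided 95% upper limit on the true rate is 1 − 0.05^(1/n), and the two-sided one is 1 − 0.025^(1/n). The values of n are the recruitment target (75) and the calculated group size (63) from the sample size section.

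| n | One-sided 95% limit | Two-sided 95% limit |
|---|---|---|
| 75 | 3.9% | 4.8% |
| 63 | 4.6% | 5.7% |

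These limits hold for any arm of that size and measure nothing specific to this trial. They show only that, at this sample size, even complete collection with no events would not establish that harm is absent.

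**The case against.** The strongest reply is that this is clumsy wording. The sentence opens with the nature of the intervention, the next sentence is hedged, and the Interim analysis section speaks of minimal risk. Read together, they may express no more than an expectation of low risk. The article is also condensed. It refers to a monitoring plan, consent forms and other documents that are not shown, and procedures for recording harms are commonly left to such documents.

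Much of this stands. A reader might infer that the trial will collect no harms data and then report that there was no harm. The article supports neither step: nowhere does it say that harms will go unrecorded, and it plans no safety claim for the final report. A reader might also infer that a woman who is harmed has no way into the safety reports. That is not shown either. There are reports to the ethics body, six-monthly reports to the auditor, a midwife visit with counselling, and opportunities for questions and feedback.

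The evidence for possible harm is limited too. The remark on blame concerns infected women, and participants are not selected for infection. The examination is offered by a trained midwife and is itself one of the preventive actions measured.

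What the reply does not remove is the sentence itself. Condensation explains silence, and the Auditing section is not silent. The hedged sentence follows the flat assertion without withdrawing it, and the conflict with the promised safety reports remains on the page.

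**Conclusion.** The point holds in a narrow form. The Auditing section states as fact what only data can show, and this conflicts with the safety reports under Ethical approval and the minimal-risk classification under Interim analysis. The reason given does not cover the genital examination or the disclosure of names, and none of the outcomes, instruments or analyses described could support the statement.

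The size is small. No harm rate can be derived from the documents, and none is claimed here. Randomization, the efficacy analysis and the sample size are unaffected; only the basis for statements about safety is touched. The conclusion rests on the article as shown. If the full protocol already records unwanted effects in both arms, only the sentence needs correcting. The article does not support saying that the trial will report no harm without collecting data.

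**What to change.** 1. In the Auditing section, replace the assertion with an expectation: the trial is considered minimal risk, and unwanted effects will be recorded in both arms. This brings it into line with the Ethical approval and Interim analysis sections.

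2. Add one item on unwanted effects, with distress and loss of privacy as examples, to the existing follow-up questionnaires in both arms. Word it so that control women can answer it too, by asking about unwanted experiences since the last questionnaire rather than effects of the training. Masking is not possible, so answers may be coloured by knowledge of the allocation, and the report should say so.

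3. Give the counts by arm in the safety reports to the ethics committee and in the final report. If none are reported, state that none were reported and how women were asked, rather than that there was no harm.

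The cost is one questionnaire item, a little coding of free text and one table. No visit is added.

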### Protocol amendment

Any changes to the study protocol, including modifications in study objectives, study design, participants population, sample size, study procedure, or significant administrative aspects that may affect the conduct of the study, potential participants’ benefit, or participants’ safety will require protocol modification. Such amendments will be agreed upon by the Department of Health Education and Health Promotion, Faculty of Medical Sciences, Tarbiat Modares University, and will be approved by the Ethics Committee of Tarbiat Modares University prior to implementation. Administrative changes of the protocol are minor corrections and/or clarifications that have no effects on the way the study is to be conducted. These administrative changes will be agreed upon by Tarbiat Modares University. The Ethics Committee of the Faculty of Medical Sciences, Tarbiat Modares University may be notified of the administrative changes at the discretion of the Department of Health Education and Health Promotion, Faculty of Medical Sciences, Tarbiat Modares University.

## Discussion

This paper describes the clinical trial protocol which will examine intervention programs to promote preventive behaviors in at-risk women. This will be the first study to examine the impact of an educational program intervention based on ISD to promote preventive behaviors from STIs in at-risk Iranian women. Women in Iran account for a high percentage of the population. Despite the high prevalence of sexually transmitted infections affecting this community, low educational interventions have been made to enable them to preventive behaviors. Therefore, this study aims to identify the educational and learning needs of at-risk women and implement a purposeful intervention program as an effective step to promote preventive behaviors regarding STIs of Iranian women aged 18–48 years. This study has several robust design features detailed as follows:Performing a randomized controlled trial based on the ISD model: This study is the first randomized controlled trial performed on women at risk of STIs to evaluate the effectiveness of the educational intervention.Theory-based intervention: The gap in the majority of intervention studies is that they are designed based on educational needs. The present study explores the effectiveness of the training intervention over an educational framework called the Instructional system design (ISD) model.

We do recognize that this study will have some limitations in so far as we must limit the randomized controlled trial to women residing in one region of Iran. This, however, will enable us to maintain good control of the test procedure. There is a possibility of not having enough access to the questionnaire link and reducing the Response-Rate. To reduce this limitation, the link of the online questionnaire will be provided to the target group with maximum variance in different ways. Another limitation of this study is the possibility of samples falling in the final intervals of the study; It seems that considering the financial cost in exchange for completing the questionnaire in four stages (pre-test, one month later, and three months after the intervention) is a good solution. Last but not least, performing educational interventions in the field of sexual health among Iranian women always faces cultural problems. Accordingly, the issue of sexually transmitted diseases is no exception to this rule. Hence, it may be difficult to accept participants to enter the study at first.

## Conclusion

This study provides an educational program for educating, empowering, and promoting behaviors that prevent sexually transmitted infections. If the interventions designed in the present study are effective, It has a high practical potential for generalization for all women aged 18-48 at risk of STIs.

### Trial status

The study is ongoing. Recruitment opened in October 2020. The duration of the study period will be 2 years and will be finished in October 2022.

## Data Availability

Not applicable. The manuscript does not report data. The datasets subsequently generated and/or analyzed during the current study may be made publicly available following the conclusion of ongoing research. Requests for data may be made at any time to the corresponding author.

## Abbreviations

STIs: Sexually transmitted infections
ISD: Instructional System Design
RCT: Randomized controlled trial
CONSORT: Consolidated Standards of Reporting Trials
